## 1. Background

Postpartum depression is a common mental disorder during puerperium. A large number of postpartum depression patients in China have not been detected. Most women have negative emotions such as depression, anxiety, fear, and pessimism. They have disharmonious relationships with their husbands and feel desperate about life. In severe cases, they may even have suicidal or infanticidal tendencies, which have serious adverse effects on the physical and mental health of women and can lead to decreased cognitive abilities of infants and an increased risk of adverse cognitive outcomes for children. This seriously threatens the health of mothers and infants and increases social health costs. Therefore, it is very important to discover, diagnose, prevent, and treat postpartum depression early.

Currently, the primary approach for treating postpartum depression is pharmacotherapy. However, most medications have a slow onset, require long-term treatment, exhibit a low clinical remission rate, are prone to chronicization, and have many residual symptoms. Addressing the shortcomings of existing antidepressants, the U.S. Food and Drug Administration (FDA) approved the first antidepressant with a novel mechanism of action, esketamine, on March 4, 2019, for the treatment of adult patients with TRD (treatment-resistant depression). Esketamine exhibits a stronger specificity for NMDA receptors, which may result in a stronger antidepressant effect. Esketamine is the S enantiomer of racemic ketamine and is primarily metabolized by CYP450. Most of its metabolites ( $\geq 78\%$ ) are excreted through urine, while a small portion ( $\leq 2\%$ ) is excreted through feces, indicating minimal impact on lactation. Numerous preclinical studies have been conducted on ketamine and its enantiomer S-ketamine (esketamine), all of which suggest that they can effectively improve depressive symptoms in mice. Multiple high-quality randomized

clinical trials (RCTs) have investigated the effect of esketamine on the PPD in women with cesarean delivery, however, the conclusions were inconsistent. Furthermore, a growing number of researchers are attempting to use meta-analysis to conclude the roles of ketamine/esketamine in PPD, and positive conclusions were exhibited in recent published meta-analysis. As a result, RCTs have become the gold standard tool for proving the efficacy and safety of treatment. However, in actual clinical practice, patients exhibit different variables, and not all patients are behaved as the representative subjects designed in RCTs. Additionally, the practice defined by RCTs significantly differs from the real-world clinical practice. All these factors may mask the effectiveness of using esketamine in PPD in actual clinical setting.

Thus, we want to conducted a pragmatic clinical trial (PCT) to explore the real clinical efficacy of intraoperative esketamine usage for preventing PPD in women undergoing cesarean section with intraspinal anesthesia. We hypothesized that patients with esketamine usage exhibited lower incidence of PPD, as measured by Edinburgh Postnatal Depression scale, compared to those without esketamine usage.

## **2. Objectives**

To explore the real clinical efficacy of intraoperative esketamine usage for preventing PPD in women undergoing cesarean section with intraspinal anesthesia.

## **3. Study design**

### **3.1 Type of study**

This study is a single-centered, double-blinded, placebo-controlled, pragmatic, clinical trial. The flow chart of study is shown as follow:

[figure not shown]

### 3.2 Sample size

A power analysis was performed based on our previous study, with the incidence of PPD at 6 weeks postpartum among pregnant women undergoing cesarean section. The incidence of PPD among subjects without esketamine was approximately 25.7%, and an expected superiority difference of 10% (one-side) in incidence of PPD between subjects with or without esketamine was used in the power calculation. To achieve a statistical power of 80% at a significant level of 0.05, it was determined that 138 patients were required in each group, and the final sample size was 154 patients considering 10% drop out. The sample size was calculated using the method of superiority by a margin test for one proportion in PASS 15.

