## **11. Statical analysis**

All analyses were conducted based on modified intention-to-treat (ITT) sample that comprised all randomized subjects received intervention and had at least one EPDS scores. Data were presented as either the mean  $\pm$  standard deviation (for normal distribution data) or median (interquartile range) (for non-normal distribution data) for continuous variables. Categorical variables were expressed as the total number (percent frequency). To compare continuous variables, the t-test was used for normal distributed data, while rank-sum test was used for non-normal distributed data. The chi-square test was employed for analyzing categorical variables, with differences of incidence of PPD between groups expressed as relative risk (RR) and 95% confidence interval (CI). Furthermore, the median difference and 95% CI of EPDS scores between groups was analyzed with the method of Hodges-Lehmann. And a subgroup analyses and sensitivity analyses will be conducted. Statistical analyses were performed in SPSS (version 17.0; SPSS Inc., Chicago, III).  $P < 0.05$  was considered statistically

significant.

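### The 138 per group rests on a one-proportion method; for the two-group comparison planned, power is about 54% (two-sided) or 66% (one-sided), not 80%

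*Protocol*

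**What the plan says.** Protocol section 3.2 gives all the inputs. On the control rate: "The incidence of PPD among subjects without esketamine was approximately 25.7" per cent. On the effect: "an expected superiority difference of 10% (one-side) in incidence of PPD between subjects with or without esketamine was used in the power calculation". On the error rates: "To achieve a statistical power of 80% at a significant level of 0.05". On the result: "it was determined that 138 patients were required in each group, and the final sample size was 154 patients considering 10% drop out". On the method: "The sample size was calculated using the method of superiority by a margin test for one proportion in PASS 15".

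Section 5 randomises 1:1 to esketamine or control. Section 8 makes PPD incidence at 6 weeks the primary outcome. Section 11 sets the comparison: "The chi-square test was employed for analyzing categorical variables", with a relative risk, a 95% confidence interval and a 0.05 threshold for P.

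**The concern.** A one-proportion test asks whether one sample differs from a rate taken as known. Here the control rate is not known; it is estimated in the control arm with as much sampling error as the esketamine arm. A method that sets that error to zero gives too small a number, and section 3.2 then uses that number as the size of each of two groups.

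This is the only power justification for the primary outcome. Section 1 motivates the trial by the inconsistent results of earlier randomised trials. If the trial ends without a significant difference, readers will weigh that result by the 80% stated. At the power the design really has, a true 10-point reduction would be missed in 46% of such trials two-sided, or 34% one-sided.

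**Working it through.** **Inputs.** From section 3.2: p1 = 0.257 (control); p2 = 0.257 − 0.10 = 0.157 (esketamine, in the direction of the hypothesis in section 1); power 80% (z = 0.842); alpha 0.05 (z = 1.645 one-sided, 1.960 two-sided); 138 per group; 10% dropout. From sections 5 and 11: 1:1 allocation, chi-square test.

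**Reproducing the plan's figure with a one-sample method.**

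n = [z_α √(p1(1−p1)) + z_β √(p2(1−p2))]² / (p1−p2)², with √(0.257 × 0.743) = 0.4370 and √(0.157 × 0.843) = 0.3638.

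- One-sided 0.05: [(1.645 × 0.4370 + 0.842 × 0.3638) / 0.10]² = 105.1, so 106.
- One-sided 0.025 (the same as two-sided 0.05): [(1.960 × 0.4370 + 0.842 × 0.3638) / 0.10]² = 135.2, so 136.
- Exact binomial at n = 138: power 81.7% for 25.7% to 15.7% at one-sided 0.025; 80.1% for 25.7% to 35.7% at one-sided 0.05; 87.0% for 25.7% to 15.7% at one-sided 0.05.

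So one-sample calculations land on or near 138, but only if one stated input is read differently (alpha halved, or the difference taken upwards). Dropout: 138 / 0.9 = 153.3, so 154, which is therefore a per-group figure.

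**Sample size for two groups.**

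n per group = [z_α √(2p̄(1−p̄)) + z_β √(p1(1−p1) + p2(1−p2))]² / (p1−p2)²

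p̄ = (0.257 + 0.157)/2 = 0.207; √(2 × 0.207 × 0.793) = 0.5730; √(0.1910 + 0.1324) = 0.5686.

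- One-sided 0.05: [(1.645 × 0.5730 + 0.842 × 0.5686) / 0.10]² = 201.9, so **202**.
- Two-sided 0.05: [(1.960 × 0.5730 + 0.842 × 0.5686) / 0.10]² = 256.5, so **257**.

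The unpooled formula gives 200 and 254; with continuity correction, 222 and 277. No two-group variant tried gives 138 at a 10-point difference.

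**Power of the two-group test.**

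Power = Φ{[(p1−p2)√n − z_α × 0.5730] / 0.5686}

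At n = 138, two-sided: (0.10 × 11.747 − 1.960 × 0.5730) / 0.5686 = 0.091, and Φ = 53.6%. One-sided: (1.1747 − 1.645 × 0.5730) / 0.5686 = 0.408, and Φ = 65.9%.

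| Evaluable per group | Two-sided 0.05 | One-sided 0.05 |
|---|---|---|
| 138 | 53.6% | 65.9% |
| 154 (no dropout) | 58.2% | 70.0% |

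Exact enumeration of the uncorrected chi-square test at 138 per group gives 53.7% and 66.2%.

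**Detectable difference at 138 per group, 80% power.** Two-sided: 13.1 points (unpooled) to 13.2 points (pooled), that is, 25.7% to about 12.5%. One-sided: about 11.9 points.

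**The case against.** Four points can be made for the plan.

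1. *The stated inputs do not give 138 by the named method either.* At one-sided 0.05 and a fall to 15.7%, the one-sample formula gives 106. This stands: the exact software settings cannot be recovered. It does not help, because the power of a two-group test at 138 per group does not depend on how 138 was reached. Nor is it likely that only the wrong module was named, since the two-group formulas give 200 to 277.

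2. *Section 3.2 says one-sided, so 66% is the fairer figure.* Section 3.2 does say so. Section 11 does not state sidedness, but a chi-square test with a 95% confidence interval and P below 0.05 is two-sided in effect. The two sections need reconciling, and both figures are given here. On the reading kinder to the plan, power is still 14 points short.

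3. *The 10% might be a superiority margin rather than the expected effect.* A further assumed effect would then be needed. None is stated, the text calls the 10% an expected difference, and section 11 tests no margin.

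4. *The missing per-group label on 154 is only an omitted word.* Agreed. The arithmetic settles it, and it needs correcting only because 154 read as a total would contradict 138 in each group.

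Section 11 already plans a relative risk with a confidence interval, so the means to report a null result properly are largely in place.

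**Conclusion.** The point holds. The 80% in section 3.2 is not a property of this design. For 25.7% against 15.7% with 138 evaluable per group, power is about 54% under the two-sided analysis that section 11 implies and about 66% under a one-sided 0.05 test. Neither the choice of sidedness nor zero dropout restores 80%. This rests on the protocol's own control rate, on the 10% being an absolute reduction, and on an uncorrected chi-square test; pooled, unpooled and exact calculations agree to within about a percentage point. What remains unknown is only how the software was set to give 138.

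**What to change.** In section 3.2, replace the one-proportion method with a calculation for two independent proportions that matches the chi-square test, and state the sidedness so that sections 3.2 and 11 agree. If enrolment stays as planned, suitable wording would be:

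> A total of 308 patients (154 per group) will be randomised, so that 138 per group are evaluable after 10% dropout. With a chi-square test at two-sided 0.05, this gives about 54% power for 25.7% versus 15.7%, and 80% power for a reduction of about 13 percentage points.

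If a one-sided test is truly intended, section 11 must say so, and the figures become about 66% power and a detectable reduction of about 12 points. A non-significant result should be interpreted through its confidence interval, not as evidence of no effect.

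The cost is rewording and a less favourable stated power; no extra patients are needed. For reference, 80% power at 10 points needs 257 evaluable per group two-sided (257 / 0.9 = 285.6, so 286 recruited) or 202 one-sided (202 / 0.9 = 224.4, so 225).

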## 4. Participants recruitment

### 4.1 Inclusion criteria

Pregnant women who were admitted for cesarean deliveries with intraspinal anesthesia were eligible.

#### **4.2 Exclusion criteria**

(1) severe cardiovascular or cerebrovascular diseases, severe gestational hypertension, preeclampsia or eclampsia;

(2) intragastric, intraocular or intracranial hypertension;

(3) uncontrolled hyperthyroidism;

(4) a history of drug abuse;

(5) intellectual dysfunction.

#### **5. Randomization and blinding**

All eligible subjects were assigned randomly to esketamine group or control group in a 1:1 ratio using a computer-generated random number sequence, and the group information was sealed in opaque envelopes. The assistant who helps to prepare the agents and outcomes assessors were blinded to the group assessments. And the anesthesiologists and healthcare team members involved in conducting cesarean delivery were not involved in the follow-up surveys.

#### **6. Groups and intervention**

After delivery of the fetus, patients received the different intervention. Esketamine group: patients received 0.25mg/kg esketamine in 20 ml of 0.9% saline for 20 minutes; Control group: patients received 20 ml of 0.9% saline for the same duration.

#### **7. Study procedures**

All the patients receive routine perioperative maternal practice. Before surgery and

anesthesia, the consent is obtained. After operation room admission, the patient is placed in a lateral position and intraspinal anesthesia is performed by an anesthesiologist. A target sensory block level is set as from T6 to T4. Vasoactive agents are used when necessary. And routine cesarean delivery is administrated with the clinical experience of obstetricians. Forceps, B-lynch suture and uterine balloon tamping are allowed to be used when necessary. After delivery of the fetus, the intervention is administrated according the groups assignment. A patient-controlled intravenous analgesia (PCIA) is provided for each patient at the end of surgery. And after surgery, the patients received routine clinical practice by the obstetricians

## **8. Primary outcomes**

The primary outcome is the incidence of PPD at 6 weeks postpartum. In this study, PPD was screened by Ediburgh Postnatal Depression Scale (EPDS, scores ranging from 0 to 30) scores of more than 10

## **9. Secondary outcomes**

The secondary outcome is the incidence of PPD at 1 weeks postpartum. EPDS scores at 1 and 6 weeks postpartum were also assessed in this study. In addition, other predefined secondary outcome includes pain intensity assessed by numerical rating scale (NRS) at 1, 2, 3 days postpartum. The pain at rest is defined as patient felt painful while lying in a supine position on the bed, while the pain with movement is considered as the patient felt painful when cough or walking on the level ground. And the PCIA agent consumption and the frequency of PCIA bolos are also recorded. The intraoperative vital signs and any adverse events are recorded. The information about

the infants is also required to be recorded.

## **10. Quality control**

All the data will be kept for at least 2 years. If any other researchers have any diabetes about this study, they can contact the corresponding authors for access to the original data. All the data related to patients will be archived and safeguarded. The protocol will be reviewed and revised by statistical experts (Pro [name], and [name]). And the visitors for the follow-up will be trained. The Ethics consent and clinical registration will be done before the trial administration.

## **11. Statical analysis**

All analyses were conducted based on modified intention-to-treat (ITT) sample that comprised all randomized subjects received intervention and had at least one EPDS scores. Data were presented as either the mean  $\pm$  standard deviation (for normal distribution data) or median (interquartile range) (for non-normal distribution data) for continuous variables. Categorical variables were expressed as the total number (percent frequency). To compare continuous variables, the t-test was used for normal distributed data, while rank-sum test was used for non-normal distributed data. The chi-square test was employed for analyzing categorical variables, with differences of incidence of PPD between groups expressed as relative risk (RR) and 95% confidence interval (CI). Furthermore, the median difference and 95% CI of EPDS scores between groups was analyzed with the method of Hodges-Lehmann. And a subgroup analyses and sensitivity analyses will be conducted. Statistical analyses were performed in SPSS (version 17.0; SPSS Inc., Chicago, III).  $P < 0.05$  was considered statistically

significant.

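### One analysis set, defined by any EPDS score, serves all analyses; it does not match the 6-week primary outcome and leaves the relative risk open to bias under some patterns of loss

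*Protocol*

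**What the plan says.** Protocol section 11 sets a single population: "All analyses were conducted based on modified intention-to-treat (ITT) sample that comprised all randomized subjects received intervention and had at least one EPDS scores". Membership has three conditions: randomised, treated, and at least one EPDS score at any visit.

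Section 8 fixes the endpoint and its time: "The primary outcome is the incidence of PPD at 6 weeks postpartum", with PPD taken as an EPDS score above 10. Section 9 gives the visits: "EPDS scores at 1 and 6 weeks postpartum were also assessed in this study". A 1-week score alone therefore satisfies the membership rule.

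Under section 11 the incidence of PPD is compared by chi-square and reported as a relative risk with a 95% confidence interval. That section adds "And a subgroup analyses and sensitivity analyses will be conducted" but does not say what these will be. Section 3.2 raises 138 per group to 154 for a 10% drop-out. The protocol does not say how a woman in the set but without a 6-week score enters the primary test.

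**The concern.** The set is tied to any EPDS score, while the primary endpoint needs the 6-week score. This has two consequences.

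- A woman seen at 1 week but not at 6 weeks belongs to the primary set, yet has no yes/no value for the chi-square test. She could be dropped, counted as a non-case, counted as a case, given her 1-week status, or imputed. These are different analyses, and the set definition does not choose between them.
- A randomised woman with no EPDS at all is removed because of something that happens after randomisation and treatment. The comparison is then no longer protected by randomisation alone.

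The outcome is depression and it is collected by a follow-up survey, so a link between mood and non-response cannot be ruled out. What is at stake is the relative risk for the primary outcome, and the freedom to choose its denominator after the data are seen. The same rule also governs pain, PCIA use and adverse events, none of which needs an EPDS score.

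**Working it through.** **Inputs.** From section 3.2: "The incidence of PPD among subjects without esketamine was approximately 25.7" (per cent), and "an expected superiority difference of 10% (one-side) in incidence of PPD between subjects with or without esketamine", which gives 25.7% on control and 15.7% on esketamine; also 138 per group and 10% drop-out. All loss patterns below are assumptions, because the documents give only the single 10% allowance.

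**The plan's own figure.** 138 / (1 − 0.10) = 153.3, rounded up to 154. This reproduces, so 154 is per group and the planned loss is 154 − 138 = 16 women per arm. How 138 was reached is a separate matter and is not used here.

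**Route A: missing women stay in the denominator as non-cases.** This assumes each of them has a 1-week score and so is in the set. With loss d in an arm, unrelated to mood, the observed rate is p × (1 − d). The observed RR is the true RR × (1 − d_esk) / (1 − d_ctrl).

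- No effect, 5% loss on control and 15% on esketamine: 0.257 × 0.95 = 0.244 and 0.257 × 0.85 = 0.218. RR = 0.85 / 0.95 = 0.89, a spurious difference of 2.6 points.
- Reversed: 0.95 / 0.85 = 1.12.
- Equal 10% loss at the planned rates: 0.257 × 0.90 = 0.231 and 0.157 × 0.90 = 0.141. RR stays at 0.61; only the risk difference shrinks, from 10.0 to 9.0 points.

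**Route B: complete cases.** If a proportion a of PPD cases and b of the others are retained, the observed rate is p·a / (p·a + (1 − p)·b).

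- If a = b within each arm, the factor cancels. Loss that depends on arm only does not bias the complete-case RR.
- No effect, esketamine arm alone losing 20% of cases and 6.5% of others: 0.257 × 0.80 = 0.2056; 0.743 × 0.935 = 0.6947; sum 0.9003, so overall loss is about 10%. Observed rate 0.2056 / 0.9003 = 0.228. RR = 0.228 / 0.257 = 0.89. If this happens in the control arm instead, RR is about 1.13.
- No effect, 90% retained everywhere except among PPD cases on esketamine: RR 0.92 if 80% of those cases are retained, 0.82 if 70%.
- The same mood-related loss in both arms (80% and 93.5% retained) at the planned rates: control 0.228; esketamine 0.1256 / (0.1256 + 0.7882) = 0.137. RR is 0.60, against a true 0.157 / 0.257 = 0.61. There is almost no bias.

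**Room left by the planned loss.** Take 154 per arm, 16 missing in each, and observed cases near the planned rates (35/138 control, 22/138 esketamine).

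| Handling of the 16 missing per arm | RR |
|---|---|
| Dropped | (22/138) / (35/138) = 0.63 |
| Non-cases in both arms | 22/35 = 0.63 |
| Cases in both arms | 38/51 = 0.75 |
| Cases in control only | 22/51 = 0.43 |
| Cases in esketamine only | 38/35 = 1.09 |

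The last two rows are outer bounds, not likely results.

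**The case against.** The strongest reply is that the protocol prescribes no biased rule. It is silent on how a missing 6-week score is handled, and imputation methods and the content of sensitivity analyses commonly sit in a statistical analysis plan, which is not shown. This stands as far as the missing detail goes. It does not cover the set definition, which the protocol itself fixes for every analysis.

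A reader might infer that any loss related to mood or to arm biases the result. The arithmetic does not support that for the RR. With complete cases, loss by arm alone does no harm, and mood-related loss that is the same in both arms barely moves the estimate. With missing counted as non-cases, equal loss leaves the RR unchanged. Material bias needs loss that differs by arm on the non-case route, or a link between loss and mood that differs by arm on the complete-case route.

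A reader might also infer that such differential loss is to be expected here. The documents give no sign of it. The control infusion is saline of the same volume and duration, the trial is described as double-blinded, outcome assessors are blinded, and follow-up staff are to be trained.

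Nor is the label misleading: the text says modified intention-to-treat and states both restrictions openly. The treatment condition is the weaker half of the concern, because a single infusion given during surgery should leave few women undosed.

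Finally, imputation is not a complete cure. It assumes missing at random. For women with no EPDS at all, the protocol lists no baseline EPDS, so the day 1 to 3 pain scores are the main named predictors. This stands, and it is why sensitivity analyses are needed.

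**Conclusion.** The mismatch is a matter of the protocol's own text: the set for the primary analysis admits women without a primary outcome and excludes randomised women on the basis of later follow-up. Whether this biases the RR depends on how missing women are handled and on the loss pattern, and neither is known. Two assumed patterns of plausible size each turn no effect into an RR of 0.89; with the arms reversed they give 1.12 and 1.13. Equal loss unrelated to mood does not bias the complete-case RR. The documents do not support a statement that the primary result will be biased, or in which direction. This is a worthwhile and cheap improvement, not a flaw that invalidates the design.

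**What to change.** Define the primary analysis on all randomised women in their assigned arm. If undosed women are to be left out, allow it only for reasons fixed before infusion and without knowledge of the arm.

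Handle a missing 6-week EPDS by multiple imputation within arm, using the 1-week EPDS and the recorded pain scores, then dichotomise at above 10. Name two sensitivity analyses: complete cases (6-week EPDS observed) and a tipping-point analysis. The latter is needed because imputation does not remove bias from loss that depends on 6-week mood itself. Pain, PCIA and adverse-event analyses should no longer require an EPDS score.

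The cost is protocol or SAP wording, a little more analysis work, and some dependence on the imputation model. No new data are needed. The wording should be settled before outcome data are seen by arm.

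### Section 11 puts every outcome on a set that needs an EPDS score, so treated women without one drop out of the vital-sign, pain, PCIA and adverse-event analyses

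*Protocol*

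**What the plan says.** Section 11 (Statical analysis) opens with a rule of universal scope: "All analyses were conducted based on modified intention-to-treat (ITT) sample". It defines that sample as one that "comprised all randomized subjects received intervention and had at least one EPDS scores". The protocol names no other population. It adds that subgroup and sensitivity analyses will be done, without saying in whom.

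Section 9 (Secondary outcomes) gives the only EPDS time points: "EPDS scores at 1 and 6 weeks postpartum were also assessed in this study". No EPDS before surgery is mentioned. The same section lists outcomes that do not depend on the EPDS:

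- "pain intensity assessed by numerical rating scale (NRS) at 1, 2, 3 days postpartum"
- "the PCIA agent consumption and the frequency of PCIA bolos are also recorded"
- "The intraoperative vital signs and any adverse events are recorded"

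On timing of treatment, section 6 says: "After delivery of the fetus, patients received the different intervention". The infusion is thus given during surgery, and section 7 has PCIA provided when surgery ends.

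**The concern.** The EPDS condition has a purpose for the depression outcomes: a woman with no score contributes nothing observed to them. For vital signs, pain, PCIA use and adverse events it has none. There it makes the use of data already in hand depend on a questionnaire due a week or more after treatment.

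Two things are at stake. First, usable data on a predefined secondary outcome (pain), and probably on PCIA use, are discarded for no gain. Second, the adverse-event summary is conditioned on something that happens after treatment. If a woman who reacts badly to the infusion is less likely to answer later contacts, the rule removes exactly the woman whom a safety summary should count. Whether that happens in this trial is not known in advance, which is a reason not to build the dependence in.

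**Working it through.** **Timing, set side by side**

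| Data | When collected | Before the first EPDS (week 1)? |
|---|---|---|
| Intraoperative vital signs | During surgery (section 9) | Yes |
| NRS pain | Days 1, 2 and 3 (section 9) | Yes |
| PCIA consumption and boluses | From the end of surgery (section 7); no end stated | Probably |
| Adverse events | No window stated (section 9) | Not fixed by the protocol |

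Section 11 ties all four rows to the EPDS condition. No sentence exempts any of them.

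**How many women the condition can remove**

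Inputs from section 3.2: 138 per group required and 10% dropout, giving 154.

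- Reproducing the plan's figure: 138 / (1 − 0.10) = 153.3, rounded up to 154. This agrees.
- Here 154 must be per group, since two groups of 138 already make 276.
- Planned loss per arm: 154 − 138 = 16.

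That 10% inflates a sample size for the 6-week outcome, so it covers loss up to week 6. A woman lost between weeks 1 and 6 keeps her week 1 score and stays in the set. A woman who misses week 1 but answers at week 6 also stays in. Only those with neither score are removed, so under the plan's own dropout figure the count per arm runs from 0 to about 16.

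**What this could do to an adverse-event rate**

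The protocol gives no adverse-event rate and nothing on who leaves early, so the following values are assumptions. Let *p* be the true rate among all 154 treated women in an arm, *m* the number with no EPDS, and *k* the leavers' rate as a multiple of *p*. The reported rate is

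*p* × (154 − *m* × *k*) / (154 − *m*).

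With *p* = 5% (7.7 women expected in 154) and *m* = 16, the upper bound:

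| *k* | Expected events among leavers | Expected events left in 138 | Reported rate |
|---|---|---|---|
| 1 | 16 × 0.05 = 0.8 | 6.9 | 5.0% |
| 3 | 16 × 0.15 = 2.4 | 5.3 | 3.8% |
| 5 | 16 × 0.25 = 4.0 | 3.7 | 2.7% |

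The ratio of reported to true rate does not depend on *p*. At *m* = 16 it is 138/138 = 1 for *k* = 1, 106/138 = 0.77 for *k* = 3, and 74/138 = 0.54 for *k* = 5.

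With half as many lost (*m* = 8), the ratios are 130/146 = 0.89 for *k* = 3 and 114/146 = 0.78 for *k* = 5, so a true 5% would be reported as about 4.5% and 3.9%. With *m* = 0, or with *k* = 1 at any *m*, there is no expected bias.

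**The case against.** The best case on the other side has four parts.

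- **Few women, and no shown bias.** The number without any EPDS may be small, and nothing in the protocol links early loss to reactions. The intervention is a single 20-minute infusion, so there is no continuing treatment to abandon because of a reaction. This stands as a limit on size: the multiples of 3 and 5 above are assumptions, and no bias is a fully possible outcome. It does not answer the exclusion itself, which follows from the text.
- **Safety sets belong in the SAP.** The absence of a named safety set would indeed be no finding. But the protocol is not silent here. It states a rule covering all analyses, and a SAP that used a different set for adverse events would contradict it.
- **The rule may have been meant for efficacy only, or an unstated preoperative EPDS might count.** The text says neither. If the first was intended, the same edit makes it clear. If the second was, most of the loss would disappear, but only the 1-week and 6-week assessments are described.
- **The conclusion on depression is untouched.** This is correct, and it keeps the point in proportion.

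A reader might also go further and infer that every adverse event predates the EPDS, that all 16 planned dropouts per arm would vanish from the safety results, or that the reported rates will favour esketamine. The documents support none of these. They set no window for adverse events, either EPDS score keeps a woman in, and the direction of any bias depends on a link between reactions and early loss that they do not show.

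**Conclusion.** The point holds as a defect in the wording of section 11. As written, women who received the infusion but have no EPDS score are excluded from the analyses of intraoperative vital signs, day 1 to 3 pain, PCIA use and adverse events. For vital signs and pain, the discarded data certainly predate any EPDS; for PCIA use this is probable; for adverse events the protocol leaves the timing open.

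The size is 0 to about 16 women per arm, taking the planned 10% as the actual loss and 154 as per group. The effect on an adverse-event rate ranges from none, when early loss is unrelated to reactions, to a fall from an assumed 5% to about 3.8% or 2.7% at the upper bound of loss, when leavers have 3 or 5 times the overall rate. The exclusion rests on the text alone; the bias rests on assumptions. The correction is worth making because it is almost free, not because a distorted safety result has been shown.

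**What to change.** In section 11, confine the EPDS condition to the EPDS outcomes (PPD incidence and EPDS scores at 1 and 6 weeks). Add one sentence saying that adverse events, intraoperative vital signs, NRS pain and PCIA use are analysed in all randomised women who received any of the study infusion and have the relevant data, whether or not they later completed an EPDS.

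Nothing wider is needed. The existing set already requires receipt of the intervention, so dropping the EPDS condition for these outcomes is enough. Nothing in the protocol argues for moving pain or PCIA use to all randomised women, including any who were not treated.

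The cost is about two sentences. No new data are collected and the primary analysis does not change. The one drawback is that denominators will differ slightly between tables, so each table should state its own.
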